# Study protocol. TRAAP - TRAnexamic Acid for Preventing postpartum hemorrhage after vaginal delivery: a multicenter randomized, double-blind, placebo-controlled trial

**DOI:** 10.1186/s12884-015-0573-5

**Published:** 2015-06-14

**Keywords:** Postpartum hemorrhage, Treatment, Prevention, Tranexamic acid, Cesarean and vaginal deliveries, Thrombosis

## Abstract

**Background:**

Postpartum hemorrhage (PPH) is a major cause of maternal mortality, accounting for one quarter of all maternal deaths worldwide. Estimates of its incidence in the literature vary widely, from 3 % to 15 % of deliveries. Uterotonics after birth are the only intervention that has been shown to be effective in preventing PPH. Tranexamic acid (TXA), an antifibrinolytic agent, has been investigated as a potentially useful complement to uterotonics for prevention because it has been proved to reduce blood loss in elective surgery, bleeding in trauma patients, and menstrual blood loss. Randomized controlled trials for PPH prevention after cesarean (*n* = 10) and vaginal (*n* = 2) deliveries show that women who received TXA had significantly less postpartum blood loss without any increase in their rate of severe adverse effects. However, the quality of these trials was poor and they were not designed to test the effect of TXA on the reduction of PPH incidence. Large, adequately powered, multicenter randomized controlled trials are required before the widespread use of TXA to prevent PPH can be recommended.

**Methods and design:**

A multicenter, double-blind, randomized controlled trial will be performed. It will involve 4000 women in labor for a planned vaginal singleton delivery, at a term ≥ 35 weeks. Treatment (either TXA 1 g or placebo) will be administered intravenously just after birth. Prophylactic oxytocin will be administered to all women. The primary outcome will be the incidence of PPH, defined by blood loss ≥500 mL, measured with a graduated collector bag. This study will have 80 % power to show a 30 % reduction in the incidence of PPH, from 10.0 % to 7.0 %.

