### Sample size

In the recent RCT (TRACOR trial), involving the same participating centers, mentioned above, comparison of the efficacy of the controlled cord traction and standard placenta expulsion in preventing PPH showed that the PPH rate (measured postpartum blood loss of 500 mL or more) was 10.0 % (402/4013), with no significant heterogeneity between centers [14].

Accordingly, for this study, we assumed a 10 % incidence of PPH in the absence of TXA. To show a relative reduction of at least 30 % in this incidence in the TXA arm—that is, an incidence of 7 % or less in this arm, with a = 0.05, 1-ß = 0.90, and a bilateral test, the study requires 1814 women with vaginal deliveries in each group. Given the expected proportion of women with a cesarean delivery in labor after randomization (estimated at 5 % to 10 % [6.8 % in the TRACOR trial] [14]), the total number of randomized women will be greater in order to include the needed number of women with vaginal deliveries: 2000 women will be included in each group, for a total of 4000 participants.

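### The abstract gives 80 % power for a reduction from 10 % to 7 %, but the trial's own sample size calculation uses 90 %, and only 90 % reproduces its 1814 women per group

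*Protocol article*

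**What the plan says.** The Methods and design paragraph of the abstract announces 4000 women, a primary outcome of measured blood loss of at least 500 mL, and this power: "This study will have 80 % power to show a 30 % reduction in the incidence of PPH". It gives the two rates as 10.0 % and 7.0 %.

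The Sample size section gives the full calculation behind the same total:

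- Control rate: "we assumed a 10 % incidence of PPH in the absence of TXA".
- Target in the tranexamic acid arm: "an incidence of 7 % or less in this arm".
- Error rates: "with a = 0.05, 1-ß = 0.90, and a bilateral test".
- Result: "the study requires 1814 women with vaginal deliveries in each group".
- Allowance: cesareans in labor after randomization are expected in 5 % to 10 % of women (6.8 % in the earlier TRACOR trial), so the number is raised to 2000 per group, 4000 in all.

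Nothing in the article explains why the two places give different powers.

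**The concern.** The outcome, the two rates and the total are the same in both places, and only the power differs. For fixed rates, test and sample size, power is determined, so at most one of the two figures can be right.

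Power is one of the headline figures that a published protocol fixes in advance. A reader who later sees a null or borderline result may ask how likely the trial was to miss a true 30 % reduction. The abstract answers one in five and the Sample size section one in ten. With both in print, either can be quoted afterwards.

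**Working it through.** **Inputs.** All come from the Sample size section: p1 = 0.10, p2 = 0.07, difference d = 0.03, two-sided alpha = 0.05 (z = 1.960), equal groups. The mean rate is p = 0.085. The normal quantiles for power are 1.2816 (90 %) and 0.8416 (80 %).

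**Formula** (pooled variance under the null, no continuity correction):

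n per group = [z_alpha × sqrt(2p(1 − p)) + z_beta × sqrt(p1(1 − p1) + p2(1 − p2))]² / d²

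The two square roots are:

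- sqrt(2 × 0.085 × 0.915) = sqrt(0.15555) = 0.3944
- sqrt(0.0900 + 0.0651) = sqrt(0.1551) = 0.3938

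**Step 1: reproduce the plan's figure at 90 %.** n = (1.960 × 0.3944 + 1.2816 × 0.3938)² / 0.0009 = 1813.95 (with unrounded terms), so **1814 per group**. This matches the stated number exactly.

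**Step 2: the abstract's 80 %.** n = (1.960 × 0.3944 + 0.8416 × 0.3938)² / 0.0009 = 1355.4, so **1356 per group**, or 2712 vaginal deliveries against the planned 2 × 1814 = 3628.

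**Step 3: could another formula give 1814 at 80 %?**

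| Method | 80 % power | 90 % power |
|---|---|---|
| Two-sided, pooled | 1356 | 1814 |
| Two-sided, unpooled | 1353 | 1811 |
| Two-sided, arcsine | 1347 | 1803 |
| Two-sided, continuity-corrected | 1422 | 1881 |
| One-sided, range over the four methods | 1061 to 1134 | 1470 to 1545 |

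No 80 % variant comes near 1814.

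**Step 4: could losses to cesarean bring 4000 women down to 80 %?** Solving the same formula for power:

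Power = Φ{[d × sqrt(n) − z_alpha × 0.3944] / 0.3938}

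| Cesareans after randomization | Analysable per group (of 2000) | Power |
|---|---|---|
| 5 % | 1900 | 91.3 % |
| 6.8 % | 1864 | 90.8 % |
| 10 % | 1800 | 89.8 % |

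The continuity-corrected version gives 88.9 % at 1814 and 88.7 % at 1800. For power to fall to 80 %, only 1356 of 2000 could remain, a loss of 1 − 1356/2000 = 32 %.

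**Step 5: what total would an 80 % design have needed?** 1356/0.95 = 1428 and 1356/0.90 = 1507 per group (rounded up), so 2856 to 3014 women in total rather than 4000.

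**The case against.** The strongest reply is that little depends on the abstract. The Sample size section is complete and correct, and neither recruitment nor the planned analysis uses the 80 %. The error also runs in the cautious direction: a trial with about 90 % power has at least 80 %, so the abstract does not hide an underpowered design. Once results are in, readers should rely on the relative risk and its 95 % confidence interval, which the Statistical analysis section provides for, more than on planned power.

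Most of this stands as a limit on the consequences. It does not make the sentence right. The abstract states the design power as a figure, not as a lower bound, and that figure contradicts the calculation on which the 4000 rests. Nor can the shortness of a journal article excuse it: that explains omissions, not two different values for one quantity.

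A narrower reply is that the powers in Step 4 treat cesarean as the only loss, although the Recruitment and allocation section foresees withdrawal or refusal after a randomization number is assigned. Power could therefore be somewhat lower than shown. That also stands, but nothing in the article suggests a total loss near the 32 % needed to reach 80 %.

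**Conclusion.** The inconsistency is real, and the abstract is the place in error. For 10 % against 7 % at two-sided 5 %, the planned 1814 vaginal deliveries per group give 90.0 % power. The 2000 randomized per group give about 90 % to 91 % over the expected range of cesareans. The abstract thus understates power by about 10 percentage points and doubles the implied type II error.

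This rests on the protocol's own rates, on an uncorrected two-proportion test, and on cesarean as the only loss from the primary analysis. A continuity correction lowers power by about one point and does not change the conclusion. The sample size, conduct and analysis are unaffected. It still needs correcting, because it is a headline design figure that the document's own calculation contradicts.

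**What to change.** In the Methods and design paragraph of the abstract, replace 80 % with 90 %. Preferably add that this refers to 1814 women with vaginal deliveries per group in the analysis, because at 10 % cesareans the 2000 randomized per group fall just short of that number (1800, power 89.8 %). The Sample size section needs no change on this point. The cost is one edited sentence, with no effect on recruitment, conduct or analysis.

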**Discussion:**

In addition to prophylactic uterotonic administration, a complementary component of the management of third stage of labor acting on the coagulation process may be useful in preventing PPH. TXA is a promising candidate drug, inexpensive, easy to administer, and simple to add to the routine management of deliveries in hospitals. This large, adequately powered, multicenter, randomized placebo-controlled trial seeks to determine if the risk-benefit ratio favors the routine use of TXA after delivery to prevent PPH.

**Trial registration:**

ClinicalTrials.gov NCT02302456 (November 17, 2014)

## Background

### Rational

#### Active management of the third stage of labor for the prevention of postpartum hemorrhage

Postpartum hemorrhage (PPH) is classically defined as blood loss of 500 mL or more after delivery [1]. Estimates of its incidence in the literature vary widely, from 3 % to 15 % of deliveries [2–5]. About one in five of these hemorrhages progresses to a severe form that may endanger the mother’s life or at least her future fertility and exposes her to the risks of transfusion, surgery, and intensive care. PPH remains a leading cause of maternal mortality and accounts for about one quarter of all maternal deaths worldwide. Its risk factors include previous PPH, primiparity, obesity, prolonged or augmented labor, multiple pregnancy, previous cesarean delivery, polyhydramnios, and macrosomia [4, 5]. Nevertheless, most women with PPH have low-risk pregnancies and no identifiable risk factors [6, 7]. It is therefore essential to prevent PPH in all women [8–11].

Because placental expulsion is a critical window for the prevention of PPH, various preventive interventions during this stage have been proposed. They can be schematically divided into two categories: those involving a mechanical mechanism, and those involving prohemostatic agents. Active management of the third stage of labor (AMTSL) comprises a combination of mechanical interventions: preventive administration of uterotonic agents immediately after delivery of the child, early cord clamping and cutting, controlled cord traction (CCT), and, according to some authors, uterine massage [12]. Nevertheless, it has been clearly shown that the administration of uterotonics, and in particular oxytocin, after birth is the only component of AMTSL that is effective in preventing PPH [13–17]. However, in addition to this enhancement of mechanical hemostasis, a complementary biochemical hemostatic effect might be expected from the complementary use of prohemostatic drugs such as tranexamic acid.

#### Tranexamic acid for the reduction of bleeding in medical contexts other than PPH

Tranexamic acid (TXA) is a potent antifibrinolytic agent that exerts its effect by blocking lysine binding sites on plasminogen molecules and has the potential to enhance the effectiveness of the patient’s own hemostatic mechanisms. Consequently, clot breakdown (fibrinolysis) is inhibited and bleeding is reduced [18]. Results from previous trials have shown that TXA in planned surgery reduces the risk of blood transfusion, mean transfused volume, and need for re-operation due to bleeding, without increasing thrombotic events [19, 20]. The CRASH-2 trial (Clinical Randomisation of an Antifibrinolytic in Significant Haemorrhage) demonstrated that the administration of TXA reduced mortality in bleeding trauma patients in high-, middle-, and low-income countries [21]. Significant reductions in mean menstrual blood loss have been reported in women with menorrhagia treated with TXA, compared with control or placebo-treated women [22]. This result is particularly significant since the efficacy of TXA in menorrhagia suggests that it can reduce uterine blood loss, even of low volume, and in a nonsurgical context [23].

#### Tranexamic acid for PPH

During delivery, when the placenta separates from the uterine wall, sequential physiologic and hemostatic changes occur and reduce bleeding, including strong myometrial contractions, increased platelet activity, and a massive release of coagulant factors; at the same time, however, fibrinolytic activity increases [24]. While oxytocin administration enhances the first mechanism, TXA administration might be able to counter the latter and thus facilitate the hemostatic process. Finally, the close relation observed between reduced fibrinogen levels and outcome in cases of PPH [25, 26] further suggests that TXA might be effective in PPH [27].

##### Treatment of PPH

The only randomized controlled trial (multicenter open-label trial) to assess TXA for the treatment of PPH showed that a high dose of TXA reduces blood loss in women with PPH [27]. Due to its limitations (small sample size, open design, issues regarding the harm-benefit ratio), and conflicting results from a before-and-after study using the same protocol [28], the use of TXA to treat PPH remains the object of debate. A pragmatic, randomized, double-blinded, placebo-controlled trial in women with a clinical diagnosis of PPH, the WOMAN trial, has been launched to rectify this clinical uncertainty [29]. It is currently recruiting eligible women in hospitals in Africa and Europe, aiming to reach the target sample size of 15 000 women [29].

##### Prevention of PPH

A Cochrane systematic review published in 2011 examined the use of TXA to prevent PPH. It identified 5 RCTs and included 2 of them in the meta-analysis, which covered a total of 453 women [18]. The authors concluded that the available evidence, although it suggested that TXA decreases postpartum blood loss, was of unclear quality and that further investigation was needed. Several additional trials have been published since then.

Through a Medline search up to March 1, 2014, we identified 12 RCTs that have assessed this issue (Tables 1 and 2) [30–41]. All were performed in low-or middle-income countries (China, India, Iran, Turkey, Pakistan, and Egypt). All but two [40, 41] only included women with cesarean deliveries. Overall, the quality of these trials was poor. Selection, performance, and detection bias might have influenced their results; in particular, the primary outcome was never the incidence of either PPH or severe PPH but rather other indicators of blood loss that may not be clinically relevant. The method used to measure the primary outcome based on estimated blood loss was often imprecise and subject to both performance and detection bias. These flaws mandate a cautious interpretation of their results [18, 42].

**Table 1 Tab1:** Characteristics of the randomized trials that have assessed tranexamic acid for preventing postpartum hemorrhage after cesarean delivery

Study [réf]	Country	Study design	Sample size	Study groups	Intervention	TXA Dosage/route	Primary outcome	Result	P value	Adverse effects
Gai et al. al, (2004) [30]	China	Multicenter, prospective, randomized controlled study	N = 180, primiparas	N = 91 (experimental)	Infusion of TXA 10 min before CS	1 g IV for 5 min	Postpartum blood loss not clearly specified	359.3 mL vs 439.3 mL	0.002	No thromboembolic or other side effects reported
				N = 89 (no placebo)						
Gohel et al., (2007) [31]	India	Prospective, randomized controlled study	N = 100, primiparas and multiparas	N = 50 (experimental)	Infusion of TXA 20 min before CS	1 g IV for 5 min	Postpartum blood loss not clearly specified	374.9 mL vs 472.8 mL	0.003	No thromboembolic or other side effects reported
				N = 50 (no placebo)						
Sekhavat et al., (2009) [32]	Iran	Prospective, randomized, placebo-controlled study	N = 90, primiparas	N = 45 (experimental)	Infusion of TXA 10 min before CS	1 g IV for 5 min	Postpartum blood loss not clearly specific	28.0 mL vs 37.1 mL	0.001	No thromboembolic or other side effects reported
				N = 45 (placebo)						
Gungorkuk et al., (2011) [33]	Turkey	Prospective, unicenter, double-blind, randomised controlled study	N = 666, primiparas and multiparas	N = 330 (experimental)	Infusion of TXA 10 min before CS	1 g IV for 5 min	Estimated blood loss during CS.	600.7 mL vs 499.9 mL	<0.001	Gastrointestinal side effects (16.3 %) in the experimental group
				N = 330 (placebo)						
										Gastrointestinal side effects not mentioned for the placebo group.
										No thromboembolic events
Movafegh et al., 2011 [34]	Iran	Prospective, unicenter, double-blind, randomized controlled study	N = 100, primiparas and multiparas	N = 50 (experimental)	Infusion of TXA 20 min before CS	10 mg/kg IV for 10 min	Postpartum blood loss not clearly specified	262.5 mL vs 404.7 mL	<0.001	No thromboembolic events
				N = 50 (placebo)						
Xu et al., 2013 [35]	China	Randomized, double-blind, placebo-controlled study	N = 174 primiparas	N = 88 (experimental)	Infusion of TXA 10 min before CS	10 mg/kg IV for 5 min	Postpartum blood loss not clearly specified	379 mL vs 441 mL	0.02	2 thromboses occurred in each group.
										Gastrointestinal side effects occurred in 10 TXA patients versus one placebo patient
				N = 86 (placebo)						
Senturk et al., 2013 [36]	Turkey	Randomized, double-blind, placebo-controlled study	N = 223, primiparas and multiparas	N = 101 (experimental)	Infusion of TXA 10 min before CS	10 mg/kg IV for 5 min	Postpartum blood loss not clearly specified	272 mL vs 347 mL	0.001	No thromboembolic or gastrointestinal side effects
				N = 122 (placebo)						
Shahid A et al., 2013 [37]	Pakistan	Randomized double-blind placebo controlled study	N = 74 primiparas and multiparas	N = 38 (experimental)	Infusion of TXA 10 min before CS	1 g IV for 10 min	Postpartum blood loss not clearly specified	356 mL vs 710 mL	<0.001	No thromboembolic side effects
				N = 36 (placebo)						
Abdel-Aleem et al., 2013 [38]	Egypt	Randomized, single center, open, controlled study	N = 740 primiparas and multiparas	N = 373 (experimental)	Infusion of TXA 10 min before CS	1 g IV for 10 min	Blood loss two hours after delivery	241.6 mL vs 510.6 mL	<0.001	Gastrointestinal side effects (74.3 % versus 53.1 %; *P* = 0.0001)
				N = 367 (no placebo)						
										No thromboembolic side effects
Goswami et al., 2013 [39]	India	Randomized, single center, double-blinded placebo controlled study	N = 90 primiparas and multiparas	N = 30 (experimental 1)	Infusion of TXA 20 min before CS	Experimental 1: 10 mg/kg	Postpartum blood loss, not clearly specified	376.8 mL vs 261.2 mL vs 527.2 mL	Not reported	No thromboembolic side effects
				N = 30 (experimental 2)						
						Experimental 2: 15 mg/kg				
				N = 30 (placebo)						

*TXA* Tranexamic acid, *IV* intravenous

**Table 2 Tab2:** Characteristics of the randomized trials that have assessed tranexamic acid for preventing postpartum hemorrhage after vaginal delivery

Study [réf]	Country	Study design	Sample size	Study groups	Interventions	TXA Dosage/route	Primary outcome	Result	P value	Adverse effects
Yang et al., (2001) [40]	China	Multicenter, randomized controlled study	N = 400 primiparas	N = 94 (experimental 1)	Infusion of TXA after delivery of the fetal shoulders in the first 2 groups and infusion of AMBA in the third	1 g IV.	Measurement of blood loss 2 h after delivery, without details about the measurement method	243.3 mL vs 242.9 mL vs 308.1 mL vs 314.8 mL	<0.01	Nausea (n = 2)
						0.5 g IV				
				N = 92 (experimental 2)						
				N = 92 (experimental 3)		0.5 g IV				
				N = 87 (no placebo)		placebo				
Gungorkuk et al., (2013) [41]	Turkey	Prospective, single-center, double-blinded, randomized controlled study	N = 439 primiparas and multiparas	N = 220 (experimental) N = 219 (placebo)	Infusion of TXA at delivery of the anterior shoulder	1 g IV for 5 min	Mean blood loss during the third and fourth stages of labor - from the end of delivery to 2 h postpartum- measured as (weight of material used – weight of materials before use)/1.05	261.5 mL vs 349.9 mL	<0.001	Gastrointestinal side effects (35.9 %)
										No thromboembolic event

*TXA* Tranexamic acid, *AMBA* aminomethylbenzoic acid, *IV* intravenous

We found 10 published RCTs evaluating the efficacy of TXA in preventing PPH after cesarean delivery [30–39]. Their characteristics are summarized in Table 1. In all but one of these studies [36], the cesareans were elective. These 10 RCTs all reported a significantly smaller mean postpartum blood loss in women who had received TXA, and no detectable adverse effect on their primary vital signs (blood pressure, heart rate, and respiratory rate) or thrombosis (Table 1) [30–39]. Nevertheless, it is important to emphasize that most of these RCTs have various methodological flaws and included small samples with inadequate power to assess the risk of adverse effects.

Only 2 trials evaluated the efficacy of TXA for the prevention of PPH after vaginal delivery [40, 41] (Table 2). In 2001, Yang al. reported a RCT comparing four groups [26]. One group (*n* = 94) received a single dose of 1 g TXA by intravenous infusion (IV), and another group (*n* = 92) a single dose of 0.5 g TXA, also IV. The third group (n =92) received a single dose of 0.5 g aminomethylbenzoic acid IV, and the fourth group (*n* = 87) served as the control group [26]. Defining PPH as blood loss ≥ 400 mL, the authors reported that its incidence was lower in the women receiving the larger TXA dose (6/94) than the control group (22/87) (Table 2). The pooled relative risk of PPH was thus RR = 0.44 (95 % CI: 0.31 to 0.64) [26, 34]. The main limitation of this study is the absence of placebo and blinding. Moreover, the randomization method was not described.

More recently, Gundorkuk et al. recruited 439 women with vaginal deliveries in a double-blinded RCT [41] (Table 2). Women in the intervention group received a single dose of 1.0 g of TXA IV at delivery of the anterior shoulder, and those in the control group a placebo. The primary outcome was the mean estimated blood loss during the third and fourth stages of labor. It was significantly lower in the TXA group than in the placebo group (261.5 ± 146.8 mL compared with 349.98 ± 188.85 mL, *P* <0.001). The incidence of PPH >500 mL was also lower in the TXA group (*n* = 4, 1.8 %) than in the control group (*n* = 15, 6.8 %); RR 3.76; 95 % CI: 1.27 to 1.15, *P* = 0.01) [41]. Moreover, the rate of total blood loss of at least 1000 mL was higher among women who received placebo (2.3 %) than among women given TXA (0.5 %), but the difference was not statistically significant (RR 5.02, CI: 0.59 to 42.64, *P* = 0.12). The groups did not differ significantly in their need for blood transfusion. Predelivery hemoglobin and hematocrit levels were the same in both groups, but the day after delivery, both hemoglobin (9.9 ± 1.4 g/dL and 9.3 ± 0.9 g/dL, *P* < 0.001) and hematocrit levels (30.2 % ± 1.2 % and 29.0 ± 1.3, *P* < 0.001) were higher in the TXA than the placebo group [41]. Finally, no episodes of thrombosis occurred in the women who received TXA. The results of this single-center trial suggest that TXA is a promising drug for the prevention of PPH after vaginal delivery and possibly for the reduction of maternal morbidity related to PPH. Nevertheless, there are again some concerns about the external validity of these results observed in a middle-income country, partly because it was a single-center study and, relatedly, because it was underpowered to assess severe adverse events.

